### Outcomes

Existing Burmese translations of measures were obtained from study authors where available. All other measures were translated into Burmese following recommended procedures including forward translation to Burmese, back translation to English by an independent translator, and consultations with bilingual team members to review and resolve any discrepancies [44]. Survey instruments were pilot tested with the target population to assess acceptability, relevance, comprehensibility, and length prior to data collection. The survey included approximately 100 items and took 1–2 hours to complete, which was deemed acceptable during piloting.

#### Primary outcomes

Physical abuse and emotional abuse will be assessed separately using items from the International Society for Prevention of Child Abuse and Neglect Child Abuse Screening Tool (ICAST-Trial; physical abuse: 4 items, range 0–32; emotional abuse: 9 items, range 0–72) [45]. Positive parenting will be assessed using an adapted version of the Parent Behaviour Inventory (PBI, 10 items, range 0–30) [46]. The PBI was previously developed and used by authors AS and EP for a trial of a family skills intervention on the Thailand-Myanmar border. These measures will be administered to caregivers at all 3 time points.

#### Secondary outcomes

Caregiver knowledge of positive parenting will be assessed by asking caregivers to indicate their agreement with 5 items developed for this study (e.g., *“Praising children is an effective way to teach children how to behave well*.*”*). Caregiver attitudes towards physical punishment will be assessed by asking caregivers to indicate their agreement with a single item from the 2015 Myanmar Demographic Health Survey (e.g., *“Do you believe that in order to bring up your child properly*, *you need to physically punish him/her*?*”*) [38], as well as 4 additional items adapted from the UNICEF Multiple Indicator Cluster Surveys [47].

Caregiver psychological distress will be assessed by the 10-item version of the Hopkins Symptom Checklist (HSCL) [48]. The HSCL has been used extensively with refugees and migrants from Myanmar [49–51]. Family functioning will be assessed with caregivers and adolescents using 6 items from the Burmese Family Functioning Scale, developed by authors AS and EP from formative qualitative research and previously used in a trial of a family skills intervention on the Thailand-Myanmar border [46]. We will also transform estimates of physical and emotional abuse into binary variables (yes/no) to investigate proportion reporting any of each type of abuse.

#### Exploratory outcomes

Caregiver coping and stress management will be assessed using 4 items drawn from the PBI (e.g., *“In the past 4 weeks until now*, *I felt too stressed to spend time with my child*.*”*) [46]. Caregiver behaviours to support early learning will be assessed using 6 items drawn from the 2015 Myanmar Demographic Health Survey (e.g., *“In the past 7 days*, *how often did you read books to or look at picture books with your child*?*”*) and administered only to caregivers of index children aged 4 to 8 years [38]. For caregivers with index children currently enrolled in school, behaviours to support education will be assessed using 6 items (e.g., *“In the last 30 days*, *how often did you praise your child for working hard at school*?*”*) adapted from Ceballo et al. [52].

To assess caregiver social support, we will use an abbreviated version of the Medical Outcomes Study Social Support Scale (MOS-SSS) consisting of 5 items from the tangible support, emotional-informational support, affectionate support, and positive social interaction support subscales [53]. The MOS-SSS was previously used in a study with Burmese adolescents living on the Thailand-Myanmar border [48]. Caregiver-reported child internalizing symptoms will be assessed by the Mood and Feelings Questionnaire (MFQ) [54], while externalizing symptoms will be assessed by the externalizing subscale of the Child and Adolescent Behaviour Inventory (CABI) [55].

#### Other measures

Sociodemographic characteristics (e.g. age, education level, length of stay in Thailand), caregivers’ lifetime trauma exposure, daily stressors, and adverse and positive childhood experiences will also be assessed to characterize the study sample and to examine potential moderators of treatment effects. Caregivers’ lifetime trauma exposure will be assessed at T0 using 6 items adapted from the Harvard Trauma Questionnaire [56]. Each item is scored as “yes” or “no” for occurrence regardless of when or where it occurred. Caregivers’ experience of daily stressors will be assessed at T0 using 9 items adapted from the Humanitarian Emergency Settings Perceived Needs Scale (HESPER) developed by the World Health Organization [57] with the addition of contextually relevant items developed from formative qualitative research. Caregivers’ adverse childhood experiences will be assessed at T2 using items adapted from the Adverse Childhood Experiences International Questionnaire (ACE-IQ) developed by the World Health Organization [58]. Caregivers’ positive childhood experiences will be assessed at T2 using items from the Benevolent Child Experiences Scale, which assesses positive early life experiences in adults with histories of adversity [59].

Finally, the endline survey at T1 will include assessment of intervention exposure (including in the control arm to assess spillover), transportation (i.e., the extent to which viewers are transported into or engaged in the narrative) [25], identification with characters, and realism and relevance of the film [60]. Participants will also be asked if they attended the film screening with other family members or discussed the film with family or community members to assess diffusion.

### Sample size calculation

The sample size calculation was performed by the trial statistician [name] and based on a two-group comparison of one of the primary outcomes (physical abuse, emotional abuse, or positive parenting) assessed at T1. Assuming a significance level of 5% with an intra-cluster correlation coefficient (ICC) of 0.02 and a two-tailed test with 0.9 power, 40 clusters with 50 caregivers per cluster would be required to detect an effect size of 0.2. The total sample size was set at 2,200 caregivers (40 clusters with 55 families per cluster) to account for up to 10% attrition. Our estimate of expected effect size was based on a review of parenting interventions for child maltreatment prevention which found an average effect of 0.2 [61]. It is possible that the number of recruited caregivers will vary in each community. We will continuously monitor realized power as we enrol caregivers into the study and stop recruitment once the harmonic mean of cluster size and number of clusters reach 90% power, or until we reach maximum capacity, whichever comes first.

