### Trial design

The study is a pragmatic, superiority cluster randomized controlled trial with approximately 40 communities (clusters) randomized to the intervention or treatment as usual (TAU) arms in a 1:1 ratio. Participating families in communities allocated to the intervention arm will be invited to attend a community screening of the film intervention and a post-screening discussion. Each family will also receive a poster depicting key messages from the film.

Primary outcomes for the trial are changes in (1) physical and emotional abuse; and (2) positive parenting behaviour. Secondary outcomes include caregiver knowledge of positive parenting, caregiver attitudes towards harsh punishment, caregiver psychological distress, and family functioning. Exploratory outcomes include caregiver coping, behaviours to support early learning and education, social support, and child internalizing and externalizing symptoms. Outcomes will be assessed at baseline prior to randomization (T0), approximately 4 weeks post-intervention (T1), and 4-month follow up (T2) (S1 File). Qualitative group interviews with caregivers and adolescents will be conducted at T1 to examine acceptability of the film-based intervention and perceived impacts on caregiver, child, and family outcomes.

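### The rule for stopping recruitment at 90% power has no attrition term, so it can use up the 10% allowance built into the 2,200 target

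*Protocol article*

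**What the plan says.** All of this stands in the protocol article under Sample size calculation. The inputs are given as "Assuming a significance level of 5% with an intra-cluster correlation coefficient (ICC) of 0.02" and "a two-tailed test with 0.9 power", for a two-group comparison of one primary outcome at T1. The result is that "40 clusters with 50 caregivers per cluster would be required to detect an effect size of 0.2". The target is then enlarged: "The total sample size was set at 2,200 caregivers (40 clusters with 55 families per cluster) to account for up to 10% attrition".

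Because communities may yield different numbers, the section adds an adaptive rule. Realized power is tracked while caregivers are being enrolled, and the team will "stop recruitment once the harmonic mean of cluster size and number of clusters reach 90% power", or stop at maximum capacity if that is reached first. The rule mentions neither attrition nor the 2,200 target. It does not say whether cluster size means caregivers enrolled or caregivers expected to provide T1 data, and it names no power formula.

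**The concern.** The step from 50 to 55 per cluster has one stated purpose: to cover loss after enrolment, so that about 50 per cluster are left at T1. The stopping rule works during enrolment, before any T1 loss can be seen, and its trigger is 90% power. If the cluster size in the rule is the number enrolled, recruitment may end at the point where 90% is reached with everyone retained. The caregivers meant to replace dropouts need never be recruited, and the later loss then takes the trial below the power at which it stopped.

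At stake is whether the 90% describes the data that will be analysed or only the sample at enrolment. The rule was live when the article was written: Trial status reports baseline complete in 33 communities, so the rule still governed the remaining ones.

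**Working it through.** **Inputs.** Two-sided alpha 0.05, ICC 0.02, effect size 0.2, 40 clusters, 50 or 55 caregivers per cluster and 10% attrition, all from Sample size calculation. Allocation is 1:1 (Trial design), so 20 clusters per arm. Assumption: the effect size is a standardised difference (SD = 1), since no SD is stated.

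**Formulas.** With m caregivers per cluster analysed:
- design effect: DE = 1 + (m − 1) x 0.02
- effective number per arm: n = 20 x m / DE
- noncentrality: λ = 0.2 x √(n/2)
- power, normal approximation: Φ(λ − 1.96)
- power, small-sample version: noncentral t with 40 − 2 = 38 df

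**1. The plan's own figure.** m = 50: DE = 1.98, n = 1,000/1.98 = 505, λ = 3.178. Power is Φ(1.218) = 88.8% (normal) or 87.2% (t). By the normal formula the effect detectable with 90% power is 0.204. The stated 90% for an effect of 0.2 is therefore reproduced within rounding.

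**2. The attrition allowance.** 40 x 55 = 2,200 enrolled, and 55 x 0.9 = 49.5 per cluster retained. Power is 88.7% (normal) or 87.1% (t), practically the 40 x 50 design. The allowance does what it was meant to do, provided that 55 per cluster are enrolled.

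**3. The rule applied to enrolled numbers.**

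| Basis of the trigger | Enrolled per cluster (total) | Left after 10% loss | Power, normal | Power, t (38 df) |
|---|---|---|---|---|
| Plan's own 90% point | 50 (2,000) | 45 | 87.2% | 85.4% |
| Exact normal 90% point | 54.2 (about 2,170) | 48.8 | 88.5% | 86.8% |
| No early stop, full target | 55 (2,200) | 49.5 | 88.7% | 87.1% |

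First row: DE = 1.88, n = 900/1.88 = 479, λ = 3.094, Φ(1.134) = 87.2%.

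With the t version as the trigger, 90% needs about 60.7 per cluster (about 2,428), so at 40 clusters the rule would not fire before 2,200.

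**4. Size of the effect.**
- From the stopping point to the analysed sample: 88.8% to 87.2% (normal) or 87.2% to 85.4% (t) for the trigger at 50, and 90.0% to 88.5% (normal) for the trigger at 54.2. That is about 1.5 to 2 points.
- Against recruiting the full 2,200: 88.7 − 87.2 = 1.5 points (normal) or 87.1 − 85.4 = 1.7 points (t) for the trigger at 50, and 88.7 − 88.5 = 0.2 points (normal) for the trigger at 54.2.

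The direction does not depend on the formula. If enrolled numbers only just reach 90%, the same formula gives less than 90% once 10% are lost.

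**The case against.** Four points can be made for the plan.

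- **Cluster size is not defined.** The reference to enrolment says when power is monitored, not what is counted. A team that has just inflated 50 to 55 might apply the same discount when monitoring. This stands in part: counting enrolled caregivers is the natural reading, not a stated one. If expected completers are meant, the text still has to say so.
- **The early stop may hardly occur.** It falls 200 short only if the trigger is the plan's rounded 40 x 50. An exact normal calculation fires about 30 caregivers short of 2,200, and a t calculation does not fire before 2,200 at 40 clusters. This stands. The allowance is fully used up only in the first case, and which case applies is unknown because no formula is named.
- **The planned analysis may recover the power.** Statistical analysis treats baseline as a repeated measure and adjusts for covariates, which the sample-size calculation does not credit. No baseline correlation r is given. If the variance is scaled by (1 − r²), an assumed r of 0.3 brings the 45-per-cluster case to 90.0% (normal) or 88.5% (t), and 0.4 to 92.2% or 90.8%. This is a fair reason to think that actual power may be adequate. It does not repair the rule, because the plan sets both its 90% and its allowance without that credit.
- **The harmonic mean already guards against unequal clusters.** True, but it addresses variation in cluster size, not loss after enrolment.

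A reader might also infer that 40 clusters of 50 do not give 90% power and that the figure should be restated as 87%. The document does not support this. The usual design-effect formula gives 88.8%, and the printed inputs are rounded: an ICC of 0.018, which also prints as 0.02, gives 90.3%. The 87% comes only from choosing a t test with 38 df, whereas the planned test is a likelihood ratio test in a mixed model.

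**Conclusion.** The point holds as a conflict within one section. The target reserves five caregivers per cluster for attrition, and the stopping rule, read as written, does not require them to be recruited. The consequence is small: after the planned 10% loss, about 87% power (normal) or 85% (t) at the earliest trigger, and about 88.5% (normal) at the exact normal trigger. This rests on cluster size meaning enrolled caregivers, on a full 10% loss spread evenly over 40 equal clusters, and on a T1 comparison without credit for baseline.

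It does not show that the stated 90% is an arithmetic error, that the allowance is lost under every formula, or that the trial will be underpowered under its planned model. It is worth correcting because the rule decides when recruitment ends and the repair is trivial.

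**What to change.** Change the rule in one of two ways, and name the power formula it uses:

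- apply it to expected T1 completers, that is, 0.9 x the enrolled size of each cluster, and stop at 90% power, at the planned 2,200 or at maximum capacity, whichever comes first; or
- keep 2,200 as the recruitment target, subject to capacity, and use the monitored power for information only.

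The cap in the first option is needed. At 40 clusters the discounted rule would ask for 54.2/0.9 = about 60 per cluster (normal) or 60.7/0.9 = about 67 (t), both above 55, so recruitment would simply run to 2,200. With more, smaller clusters the rule can still operate: 44 clusters of 50 (2,200) leave 45 each after 10% loss, n = 22 x 45/1.88 = 527 per arm, λ = 3.245, and normal power is 90.1%.

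The cost is one line of text. Recruitment may continue to the already planned 2,200 where it would otherwise have stopped earlier, by at most 200 caregivers at 40 clusters. Nobody beyond the planned sample is needed, and the stated 90% for 40 x 50 can stay.

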### Statistical analysis

Trial results will be reported following the updated recommendations of the Consolidated Standards of Reporting Trials (CONSORT) 2010 statement: extension to cluster randomised trials [62]. Initial analyses will compare baseline characteristics of participants across the two study arms as well as participants who completed T1 assessments and those who did not.

#### Caregiver analyses

Outcomes will be analysed using three-level models with measurement wave within participant within cluster where outcomes are measured over multiple timepoints. Level 1 will include a term for categorical time (T1 and T2) and the interactions between intervention and categorical time; level 2 will include terms for caregiver and child age and gender, centred at the sample mean; and level 3 will include terms for intervention and stratification. Thus, the estimate of intervention effectiveness is the interaction between intervention and categorical time. A likelihood ratio test against a model without interactions will form the test of effectiveness. The primary analysis is from an imputed and adjusted model, which will generate differences in the primary outcomes between the two study arms at T1 and T2 using 95% CIs. Crude (i.e. models including intervention, time, intervention by time interactions, and stratification) imputed and unimputed models will be used for sensitivity analysis.

Primary analyses will be conducted using the intention to treat principle. To account for dropouts in the intention-to-treat analysis, the baseline measurement will be treated as a repeated measure and estimation of the intervention effects will be via maximum likelihood. The impact of the missing data on the estimated intervention effect will be assessed by imputing missing outcome data (at least 10 imputations, using an unrestricted multilevel model with fully conditional specifications) using complete baseline and follow-up data and running the same models. Per-protocol analyses will also be conducted using only the data on participants who received the intervention as planned. All additional analyses, including analysis of potential moderators and mediators, will be detailed in a statistical analysis plan prior to unblinding. Across all analyses, two-tailed tests will be reported with a significance level of p<0.05.

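### The primary model names no cluster-by-time random effect; fitted with random intercepts only, its test of effectiveness would leave community-level differences in change out of the standard error

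*Protocol article*

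**What the plan says.** The Caregiver analyses section sets out the primary model level by level. The nesting comes first: "Outcomes will be analysed using three-level models with measurement wave within participant within cluster". On the lowest level, "Level 1 will include a term for categorical time (T1 and T2) and the interactions between intervention and categorical time". The participant level carries caregiver and child age and gender. At the community level, "level 3 will include terms for intervention and stratification". Time therefore appears at level 1 only.

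The effect is a contrast of changes: "the estimate of intervention effectiveness is the interaction between intervention and categorical time", and "the baseline measurement will be treated as a repeated measure and estimation of the intervention effects will be via maximum likelihood". The test is fixed too: "A likelihood ratio test against a model without interactions will form the test of effectiveness". With T0, T1 and T2 all in the model, this test has 2 degrees of freedom.

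The section leaves additional analyses, such as moderators and mediators, to a statistical analysis plan. It does not say the same of the primary model. Clustering is quantified only in the Sample size calculation section, for a two-group comparison at T1: "Assuming a significance level of 5% with an intra-cluster correlation coefficient (ICC) of 0.02".

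**The concern.** Communities are randomised, so the uncertainty of the effect has to include how much communities differ, for reasons unrelated to the film, in the quantity being compared. That quantity is change from baseline. A community intercept that is constant over time describes differences in level and drops out of any change. If it is the only community-level random term, the interaction is judged against the participant-level residual alone, much as if caregivers had been randomised individually. Communities whose reported parenting moves differently from T0 to T1 or T2 would not be reflected in the standard error.

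The same model serves physical abuse, emotional abuse and positive parenting. At stake is whether the intervals and p-values for all three are too narrow and too small, so that community-level variation in change could be read as an effect of the film.

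**Working it through.** **Inputs from the article.** 40 communities, 1:1, so 20 per arm; 50 caregivers each at analysis; ICC 0.02; two-sided 5%; effect size 0.2; power 0.90; three waves.

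**Assumed inputs, not in the article.** Cluster autocorrelation (CAC), the correlation of a community's effect between waves, 0.5 to 1.0. Participant autocorrelation (IAC), 0.3 to 0.7. Total variance is 1, data are complete and balanced, and the ICC is the same at each wave.

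**Step 1: the plan's own figure.** Design effect = 1 + 49 × 0.02 = 1.98. Effective n per arm = 1000/1.98 = 505. Standard error = √(2/505) = 0.0629, and 0.2/0.0629 = 3.18. Power by the normal approximation is 0.888, close to the stated 0.90 (0.872 with t on 38 df). The design therefore allows for clustering in a T1 comparison.

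**Step 2: what survives in a change.** Split the outcome into a stable community effect, a community-by-wave effect with variance s²ct = 0.02(1 − CAC), a stable participant effect, and a residual with variance s²e = 0.98(1 − IAC). Both stable effects cancel from T1 minus T0. For the difference between arms in change:

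- True variance = 4 × [s²ct/20 + s²e/1000].
- Variance under random intercepts only = 4 × [s²ct + s²e]/1000, because the community-by-wave variation is absorbed into the residual and treated as independent between caregivers.
- Ratio R = (s²e + 50 s²ct)/(s²e + s²ct).

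Equivalently, R = 1 + 49 × (ICC of the change).

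**Step 3: numbers at IAC 0.5 (s²e = 0.49).**

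- CAC 0.9: R = (0.49 + 0.10)/0.492 = 1.20; ICC of the change 0.002/0.492 = 0.004.
- CAC 0.8: R = (0.49 + 0.20)/0.494 = 1.40; ICC of the change 0.004/0.494 = 0.008.
- CAC 0.5: R = (0.49 + 0.50)/0.500 = 1.98; ICC of the change 0.01/0.50 = 0.02.

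**Step 4: type I error of the 2-df test.** Under the null the statistic behaves as R times a chi-square on 2 df, so the error is exp(−5.991/(2R)). Entries are R and error at ICC 0.02:

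| CAC | IAC 0.3 | IAC 0.5 | IAC 0.7 |
|---|---|---|---|
| 1.0 | 1.00, 5.0% | 1.00, 5.0% | 1.00, 5.0% |
| 0.95 | 1.07, 6.1% | 1.10, 6.6% | 1.17, 7.7% |
| 0.9 | 1.14, 7.3% | 1.20, 8.2% | 1.33, 10.5% |
| 0.8 | 1.28, 9.7% | 1.40, 11.7% | 1.66, 16.4% |
| 0.5 | 1.70, 17.2% | 1.98, 22.0% | 2.61, 31.8% |

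For the single T1 contrast at IAC 0.5 the error is 7.3%, 9.7% and 16.4% at CAC 0.9, 0.8 and 0.5. With an ICC of 0.01 and IAC 0.5, the 2-df values are 6.5%, 8.2% and 13.4%.

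**Step 5: simulation.** 2,000 null trials per setting (40 × 50, three waves) gave 8.6%, 11.1% and 23.2% at IAC 0.5 and CAC 0.9, 0.8 and 0.5, with a Monte Carlo standard error of about 0.5 points near 5%. At CAC 1.0 the result was 5.4 to 6.4% over the three IAC values. An F test against the cluster-by-time stratum gave 5.1 to 6.6% on the same data, so this is simulation noise and not a systematic excess. The closed-form likelihood ratio matched mixed-model maximum likelihood fits on two test data sets.

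**Step 6: with cluster-by-time variance in the error term.** Simulated error was 4.3 to 6.6% over all settings. Power for 0.2 on T1 minus T0 uses the true variance of Step 2 and t on 38 df. At IAC 0.5:

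- CAC 0.9: variance 4 × (0.0001 + 0.00049) = 0.00236, power 0.98.
- CAC 0.8: variance 4 × (0.0002 + 0.00049) = 0.00276, power 0.96.

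At CAC 0.5, power is 0.81 to 0.93 over IAC 0.3 to 0.7.

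**The case against.** The strongest reply is that the section gives the nesting and the fixed terms but lists no random effects and excludes none. A three-level model can carry a community-level random coefficient for time. A reader might infer that the planned model has no cluster-by-time variance; the article does not say so. That stands. What remains is that the primary model is set out in detail here, only additional analyses are deferred, and the usual fit of the described nesting is random intercepts.

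A reader might also infer that the error rate exceeds 5% whatever happens. It does not: with perfectly stable community effects it is 5%, and any excess depends on two autocorrelations that the article does not give.

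Nor does the article support an argument from a highly mobile population. Its section on communities says that movement between them tends to be limited, and the same caregivers are followed at all three waves. Neither fact establishes perfect stability, but neither points to large drift.

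The design effect of 1.98 is not by itself a sign of error. It belongs to a cross-sectional T1 comparison, and the stable part of the ICC ought to cancel from a change. Only the unstable part is at issue.

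Finally, one might count the chi-square reference with about 40 randomised units as a separate fault. Under random intercepts only, the interaction is tested against a residual with thousands of degrees of freedom, and the chi-square reference is accurate for that model. The small number of communities matters only once the cluster-by-time term is included.

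**Conclusion.** The point holds in conditional form. The article names no cluster-by-time random effect for a test that is entirely a contrast of changes between randomised communities. If none is fitted, the test keeps its 5% level only when communities do not differ in change. At the protocol's ICC of 0.02 and 50 per cluster, with the middle assumption of participant autocorrelation 0.5, the 2-df error is about 8%, 12% and 22% at cluster autocorrelation 0.9, 0.8 and 0.5. An ICC of the change as small as 0.004 is enough for the first of these.

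The sizes rest on assumed autocorrelations and on balanced, complete data. The direction does not depend on the values chosen, provided the cluster autocorrelation is below 1. The design is not in doubt: power remains adequate at cluster autocorrelation 0.8 to 0.9 when the term is included.

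**What to change.** State the random effects of the primary model before unblinding. Include, besides the participant and community intercepts, a community-by-wave random effect or an unstructured community-level covariance over T0, T1 and T2.

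With that term in the model, base inference on the roughly 40 communities. One way is a small-sample degrees-of-freedom correction (Satterthwaite or Kenward-Roger, with REML and an F test of the interaction terms). Another is to keep the likelihood ratio test and add a community-level analysis of change as a sensitivity check. The choice between these is partly preference; the variance term is the essential change.

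The cost is one sentence, one more variance component and wider intervals. At participant autocorrelation 0.5 the standard error grows by about 10% (√1.20) at cluster autocorrelation 0.9 and 18% (√1.40) at 0.8. If the estimated component is close to zero, little is lost.

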Sermpanya Foundation will conduct mobile screenings of the film in community locations that can accommodate large groups and that are accessible and safe for migrant and displaced families. Study participants and their families will be invited to attend the film screening and attendance will be tracked to assess intervention exposure. Other members of the same community will also be able to attend; however, individuals residing in other communities will not be admitted to minimize spill over. Immediately after the film screening, trained facilitators from local partner organizations will lead a structured discussion with audience members to reinforce the key messages and skills depicted in the film. The audience discussion will last approximately 45 minutes, after which the audience will be shown a 5-minute video featuring two community advocates summarizing the key messages from the film and audience discussion. Finally, each household will receive a poster depicting key messages.

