#### Treatment as usual (TAU)

TAU will consist of providing study participants with information about existing services related to child protection and safeguarding and related education and health services in Tak province. In collaboration with local partners, we developed a list of services with brief descriptions including information on how to access services. Caregivers in both the intervention and control groups will receive this information via handouts distributed at the time of the baseline assessment. Caregivers’ participation in any other parenting-related interventions or services during the study is permitted and will be assessed at endline (T1).

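### The supplementary per-protocol analysis selects on voluntary attendance after randomisation, so it is a non-randomised contrast whose bias has unknown size and direction

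*Protocol article*

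**What the plan says.** The relevant text is in the Protocol article under Statistical analysis, Caregiver analyses. The main analysis is clear: "Primary analyses will be conducted using the intention to treat principle". A supplementary analysis is then added: "Per-protocol analyses will also be conducted using only the data on participants who received the intervention as planned". That sentence does not mention controls.

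On how the film reaches caregivers (Film-based intervention): "Study participants and their families will be invited to attend the film screening and attendance will be tracked to assess intervention exposure". On the control condition (Treatment as usual): "Caregivers in both the intervention and control groups will receive this information via handouts distributed at the time of the baseline assessment". Both arms therefore get the handout before allocation, and only intervention communities get the invitation.

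On the model: "the estimate of intervention effectiveness is the interaction between intervention and categorical time"; for the intention-to-treat analysis, "the baseline measurement will be treated as a repeated measure and estimation of the intervention effects will be via maximum likelihood"; and for covariates, "level 2 will include terms for caregiver and child age and gender, centred at the sample mean", plus stratification. All analyses are tested two-sided at 5%. Further detail is deferred: "All additional analyses, including analysis of potential moderators and mediators, will be detailed in a statistical analysis plan prior to unblinding". Under Other measures, exposure to the film is asked at T1 in both arms.

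**The concern.** Baseline assessment precedes randomisation, and attendance follows it. Receipt is thus a post-randomisation choice that only one arm is offered. Restricting one arm to those who made that choice leaves nothing in the other arm to match it, because the controls who would have come if invited cannot be identified.

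Selection is plausible in this setting. The film, discussion and closing video take about 66 + 45 + 5 = 116 minutes. The article describes families without legal status who cannot move freely (Communities), insecure and exploitative work (Study setting), and a link from displacement stress and parental distress to violence in the home (Background and rationale). Age and gender of caregiver and child do not capture these factors. As described, they also enter as main effects, which adjust level rather than change over time.

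At stake is a second set of effect estimates with confidence intervals and p-values that randomisation does not protect.

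**Working it through.** **Inputs from the article.** 40 clusters randomised 1:1, 50 evaluable caregivers per cluster, ICC 0.02, effect 0.2 SD, two-sided 5%, power 0.90 (Trial design; Sample size calculation). No uptake figure and no attender/non-attender difference is given, so p and d below are assumptions.

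**1. The plan's own figure.** The design effect is 1 + 49 × 0.02 = 1.98. Effective n per arm is 20 × 50 / 1.98 = 505. The standard error is √(2/505) = 0.0629 SD. Power is Φ(0.2/0.0629 − 1.96) = 0.888 against the stated 0.90. This is close enough, and it does not bear on the point except to supply the 0.2 SD yardstick and the standard error.

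**2. Bias of attenders against all controls.** Let p be the share attending and d the attender minus non-attender difference, in SD, in whatever untreated quantity is analysed (outcome or change). With no true effect, the control mean is p × attender mean + (1 − p) × non-attender mean, so attender mean minus control mean = (1 − p) × d.

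The chance that a nominal 5% test rejects under no effect uses SE = √{[1 + (50p − 1) × 0.02]/(20 × 50p) + 1.98/1000}. At p = 0.7 this is √(1.68/700 + 0.00198) = 0.0662. Each cell gives bias in SD, then rejection probability:

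| p | d = 0.1 | d = 0.2 | d = 0.3 | d = 0.5 |
|---|---|---|---|---|
| 0.5 | 0.05; 0.11 | 0.10; 0.296 | 0.15; 0.569 | 0.25; 0.945 |
| 0.7 | 0.03; 0.074 | 0.06; 0.148 | 0.09; 0.275 | 0.15; 0.62 |
| 0.9 | 0.01; 0.053 | 0.02; 0.061 | 0.03; 0.076 | 0.05; 0.123 |

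The bias is zero only if everyone attends or d = 0. The rejection probabilities assume unit variance and ICC 0.02 for the analysed quantity.

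**3. What the planned model changes.** With an arm main effect and baseline as a repeated measure, the intervention-by-time interaction is, for complete data, a difference in mean change. So d must be read as a difference in change, not in level. A simulation (no true effect, 40 × 50 caregivers, ICC 0.02, 70% attendance, within-person correlation 0.3 to 0.7, attendance correlated 0.3 with its driver, higher score better) gives:

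| Attendance driven by | Bias, T1 level (SD) | Bias, change from baseline (SD) |
|---|---|---|
| Stable trait | 0.07 to 0.13 | about 0 |
| Observed baseline score | 0.04 to 0.11 | −0.10 to −0.04 |
| Readiness to change | 0.06 to 0.08 | +0.12 to +0.18 |

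Stable differences cancel. Selection on the baseline score leaves regression to the mean, and selection on change stays in full. If caregivers with worse baseline scores were the ones who attended, the sign in the second row would reverse.

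**4. The alternative, tested the same way.** With no control attendance, the complier-average estimate is the intention-to-treat effect divided by p. If non-attenders gain e through posters or talk, it is inflated by e(1 − p)/p. At p = 0.7, e = 0.05 this is 0.05 × 0.3/0.7 = 0.02 SD; at p = 0.5, e = 0.1 it is 0.10 SD (assumed values). Its standard error at p = 0.7 is about 0.0629/0.7 = 0.090, against 0.066 for the per-protocol contrast.

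**The case against.** **It is supplementary.** This stands. A reader might infer that the trial's conclusion is compromised, or that the per-protocol figure will be put forward as the effect of seeing the film, especially if uptake is low. The article gives that analysis no such role, and the primary result does not depend on it.

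**The detail belongs in the analysis plan, which is not shown.** This stands in part. The definition of adequate receipt, the handling of controls and any adjustment may be set there, and their absence from the article is no fault. But the article already fixes the restriction to recipients, and later detail does not undo that. That controls are kept whole is an inference; the sentence does not say so.

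**Receipt can be seen in controls.** A reader might infer that exposure is recorded only in the intervention arm. It is not: the T1 survey asks both arms. A natural reading is therefore attenders against unexposed controls. What remains unobservable is which controls would have attended if invited, so that reading is non-randomised too.

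**The simple bias formula overstates the problem.** This stands if d is taken as a difference in level. Work, mobility and general motivation may be fairly stable, and the planned model would then remove most of their effect. A reader might also infer that the bias flatters the film. The documents do not support a direction, and plausible mechanisms give either sign.

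**The complier-average estimate has its own weak point.** This stands. Each family receives a poster, other household and community members may attend, and discussion of the film is measured as diffusion. Non-attenders may therefore be partly treated, and the resulting error can match the one being avoided.

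**Conclusion.** The point holds in a limited form. The per-protocol set depends on a choice made after randomisation that has no counterpart in controls. Any workable version is an observational comparison, and the literal version has no comparator.

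The size cannot be stated from the article. Over assumed attendance of 0.5 to 0.9 and d of 0.1 to 0.5 SD in the analysed quantity, the bias runs from 0.01 to 0.25 SD, or 5% to 125% of the 0.2 SD design effect. If the planned model is reused and selection is on stable traits, it is near zero; if selection is on baseline score or on change, it is not, and its sign is unknown. The change should be made before unblinding, but the matter is moderate because the intention-to-treat analysis is untouched.

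**What to change.** Keep intention to treat as primary. In the analysis plan, make the as-received estimate a complier-average causal effect:

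- community allocation as the instrument for attendance, taken from screening records and the T1 question asked in both arms;
- all randomised caregivers kept, with the same covariates as the main model;
- inference that allows for clustering.

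State the exclusion restriction and report sensitivity to it, for example over a range of assumed gains in non-attenders using e(1 − p)/p. State also that the method deals only with controls who actually attended, not with those who heard about the content.

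If the per-protocol contrast is also reported, define what counts as receipt as planned, name the comparator, and label the result non-randomised.

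The cost is some wording and one further model on data already being collected. The downsides are a wider interval and reliance on an assumption that posters and diffusion make doubtful.
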